Major hypoglycaemia	A hypoglycaemic episode in which the patient is not able to treat themselves and in which oral carbohydrates, glucagon or intravenous glucose has to be administered to the patient by another person because of severe central nervous system dysfunction
Neonatal death	Death of an infant between 7 and 28 completed days after delivery
Perinatal death	Death of a foetus/infant at ≥22 completed gestational weeks and <1 completed week after delivery
Preterm delivery	Delivery before 37 completed gestational weeks
Pre-eclampsia	A condition in pregnancy characterised by new onset of abrupt hypertension (≥140/90 mmHg documented on two occasions, ≥6 h and ≤7 days apart) and proteinuria/albuminuria
Spontaneous abortion	A naturally occurring termination of a pregnancy before 22 completed gestation weeks

The study has a fixed recruitment period of 5 years (September 2013 to September 2018), and will include gestation and follow-up of infants at 1 month and 1 year of age. The planned enrolment is 3055 patients.

The study population will include women with T1D or T2D (as assessed from maternal medical history) who are pregnant and being treated with insulin or other injectable antidiabetic treatment regimens, and who have not changed their basal insulin or other injectable antidiabetic treatment for 4 weeks prior to and following conception. Inclusion and exclusion criteria are listed in Table 2.

**Table 2 Tab2:** Inclusion and exclusion criteria

Inclusion criteria
• Woman with a positive pregnancy test
• Type 1 diabetes or type 2 diabetes, diagnosed prior to conception
• Treated with unchanged basal insulin or other injectable antidiabetic treatment (for those not treated with basal insulin) for 4 weeks prior to and following conception
• Informed consent obtained before any data collection
Exclusion criteria
• Women who have been pregnant for >12 weeks at baseline visit confirmed by ultrasound

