### Statistical considerations

The analysis set will consist of all pregnancies among patients who are treated with basal insulin and have not changed basal insulin product for 4 weeks prior to conception and during pregnancy. Continuous variables will be summarised with descriptive statistics, and categorical variables will be displayed in frequency tables.

The primary endpoint will be analysed using a logistic regression model that will include treatment group, study site, race, hypertension, major hypoglycaemic events during pregnancy, folic acid intake and use of GLP-1 agonists during pregnancy as factors. HbA_1c_ at the start of pregnancy, the end of the first trimester and the end of the second trimester, age and body mass index at baseline, duration of diabetes, blood pressure and previous perinatal complications will be included as covariates. The primary endpoint will be computed for the IDet group and for the ‘other basal insulin’ group and the absolute difference between these proportions calculated, along with the 95% CI and the *p*-value using Fisher’s exact test.

For infant endpoints at 1 year, the proportions will also be analysed using logistic regression. Factors and covariates will be as per the primary endpoint. Analyses regarding height and weight will also be adjusted for exclusive and/or partial lactation period. Similar analyses will be performed for all other endpoints that are proportions.

Means of the continuous endpoints will be compared between the two groups using an analysis of covariance model.

The incidence of major hypoglycaemia during pregnancy will be computed for both treatment groups.

Observations of possible clinical importance (such as the primary endpoint split out according to diabetes type, insulin analogue or use of an insulin pump) will be presented using descriptive statistics.

All statistical analyses will be performed using appropriate statistical software, and tests will be performed as two-sided tests with a significance level of 0.05.

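### The adjusted models include previous perinatal complications but no parity term, so first-birth status remains a potential confounder in a non-randomised comparison

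*Protocol article*

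**What the plan says.** Under Statistical considerations, the protocol article names the factors of the primary logistic model: "treatment group, study site, race, hypertension, major hypoglycaemic events during pregnancy, folic acid intake and use of GLP-1 agonists during pregnancy as factors". The covariates are HbA1c at three time points and then: "age and body mass index at baseline, duration of diabetes, blood pressure and previous perinatal complications will be included as covariates". Neither list contains parity, gravidity or an indicator for first birth.

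The model is carried further. For the infant endpoints at 1 year, "Factors and covariates will be as per the primary endpoint". The remaining endpoints that are proportions are to be analysed similarly. Under Study endpoints these include pre-eclampsia, fetal macrosomia, large for gestational age and preterm delivery.

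Table 2 sets no condition on obstetric history. The inclusion criterion on pregnancy is "Woman with a positive pregnancy test", and the only exclusion listed is "Women who have been pregnant for >12 weeks at baseline visit confirmed by ultrasound".

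Besides the model, the plan compares the crude proportions for the primary endpoint, with "the absolute difference between these proportions calculated" together with its 95% CI and a Fisher's exact p-value.

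**The concern.** A history of perinatal complications presupposes an earlier pregnancy that reached the perinatal period. Table 1 defines perinatal death as "Death of a foetus/infant at ≥22 completed gestational weeks and <1 completed week after delivery". On that definition, a woman in her first pregnancy has no perinatal history, and neither does a woman whose earlier pregnancies all ended before 22 completed weeks. Both kinds of women can enrol.

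The covariate is listed with age, body mass index and blood pressure, apart from the factors, and so reads as a single term. Such a term has one contrast, complications or none. Women without a previous birth then share the value for none with women who had an uncomplicated birth. If the two kinds of women differ in risk, and if their mix differs between the insulin groups, part of the difference between groups is due to birth history and the model cannot remove it.

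Treatment follows current practice and is not randomised, so the adjusted models carry the control of confounding. Birth order is most plausibly relevant to pre-eclampsia, birth weight and preterm delivery, and probably less so to the primary composite.

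**Working it through.** **1. The plan's own figures.** From Determination of sample size: component rates 4.5%, 3% and 0.9%. Under independence, the combined rate is 1 − 0.955 × 0.970 × 0.991 = 0.0820, so 91.8% are event-free, as stated.

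Sample size for 95.3% (insulin detemir) vs 91.8% (other), 1:2 split, two-sided 5%, 80% power, with k = 2 and pooled proportion (0.953 + 2 × 0.918)/3 = 0.9297:

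n₁ = [1.96 √(p̄q̄(1 + 1/k)) + 0.8416 √(p₁q₁ + p₂q₂/k)]² / 0.035² = [1.96 × 0.3132 + 0.8416 × 0.2871]² / 0.001225 ≈ 598

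The total is 3 × 598 = 1794, within 3% of the stated 1833. At 611:1222 the power is 0.81. This figure is not in dispute.

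**2. What a single term leaves uncontrolled.** All inputs in this step are assumptions, because the documents give no parity data.

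- Risk of the primary composite after a previous uncomplicated birth: r = 7%, chosen to lie near the plan's 8.2%.
- Share of women with a previous birth who had complications: 15%. The stratum coded as no complications therefore holds all women without a previous birth and 85% of the others.
- Odds ratio for no previous birth vs previous uncomplicated birth: 1.2, 1.5 or 2.0.
- Share f of women without a previous birth in each group: as tabulated.

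Formulas, within the stratum coded as no complications:

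- share without a previous birth: q = f / (f + 0.85(1 − f))
- their risk: rₙ = o/(1 + o), with o = OR × 0.07/0.93
- stratum risk in a group: q rₙ + (1 − q) × 0.07

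Upper end (OR 2.0, 60% vs 40%): o = 0.1505 and rₙ = 0.1308; q = 0.638 and 0.440; stratum risks 0.1088 and 0.0967. The difference is 1.21 points and the odds ratio is (0.1088/0.8912)/(0.0967/0.9033) = 1.14.

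Lower end (OR 1.2, 50% vs 40%): o = 0.0903 and rₙ = 0.0828; q = 0.541 and 0.440; stratum risks 0.0769 and 0.0756. The difference is 0.13 points and the odds ratio is 1.02.

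Spurious odds ratio with no insulin effect:

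| First-birth OR | 50% vs 50% | 50% vs 40% | 55% vs 45% | 60% vs 40% |
|---|---|---|---|---|
| 1.2 | 1.00 | 1.02 | 1.02 | 1.04 |
| 1.5 | 1.00 | 1.04 | 1.04 | 1.08 |
| 2.0 | 1.00 | 1.07 | 1.07 | 1.14 |

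**3. A secondary endpoint.** For pre-eclampsia, assume a risk of 20% without and 10% with a previous birth (an odds ratio of 0.25/0.111 = 2.25), and shares of 50% vs 40%. This is a crude mix that sets previous complications aside. The group risks are 0.5 × 20% + 0.5 × 10% = 15.0% and 0.4 × 20% + 0.6 × 10% = 14.0%. The difference is 1.0 point and the odds ratio is (0.15/0.85)/(0.14/0.86) = 1.08.

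Steps 2 and 3 allow for no other term in the model. Age, body mass index, diabetes duration and blood pressure may absorb part of any such effect.

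**The case against.** The strongest reply is that coding belongs to the full protocol or the analysis plan. The article does not say how the covariate is coded, and a three-level coding under the same name would already separate the groups. This stands as far as coding goes: missing detail is not an error. It does not cover the choice of terms, which the article fixes one by one without parity. Nothing in the text points to a three-level reading.

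A reader might infer more: that women without a previous birth have a missing value and fall out of the regression. With an assumed 35% to 50% of such women, 1191 to 917 of the 1833 pregnancies would remain, and approximate two-proportion power would fall from 0.81 to between 0.61 and 0.50. The arithmetic is right, but the documents do not support the premise. The article nowhere says that these women are dropped or coded as missing. The 1833 also serves the crude difference and Fisher's test, which use no covariates and lose no woman. The power loss is therefore not part of this point.

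Three further objections limit its size. No passage shows that the choice of insulin varies with birth history, and without such variation there is no bias. The pre-eclampsia example is a single assumed scenario for a secondary endpoint. The sentence carrying over the covariates is attached to the infant endpoints; for the other proportions the article promises only similar analyses, so an identical covariate set is likely but not stated. All three stand.

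**Conclusion.** The point holds in a limited form. The listed adjustment set cannot separate women with no previous birth from those with a previous uncomplicated birth if the complications term is a single one, as its place among the covariates suggests. First-birth status then remains an uncontrolled potential confounder in the adjusted models.

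The likely effect is modest: a spurious odds ratio of about 1.02 to 1.14 (0.1 to 1.2 percentage points), and none if first-birth shares are equal between groups. That range rests wholly on the assumed shares, odds ratios, 7% risk and 15% complication share set out above. The Fisher comparison does not depend on the covariate; being unadjusted, it also cannot make up for the gap. The stated sample size and its power are not called into question here.

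**What to change.** Replace previous perinatal complications by one three-level factor:

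1. no previous birth at 22 or more completed gestational weeks;
2. at least one such birth, none with perinatal complications;
3. at least one such birth with perinatal complications.

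Use it in the primary model and wherever that model is reused, and state whether the other proportion endpoints take the same covariates. Define the levels by previous birth, not by first pregnancy. Otherwise a woman with only earlier losses before 22 weeks would be placed with women who had an uncomplicated birth.

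The cost is one extra parameter in a model that already has many terms. The obstetric history needed to fill the existing covariate should supply the three levels, so little or no new data collection should be needed.

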## Methods/design

This study is an international, prospective, non-interventional, multicentre cohort study to monitor and assess the safety of IDet in comparison with other types of insulin treatment during pregnancy, and to monitor the health status of the resulting infants (who were exposed in utero) at 1 month and 1 year of age. The large-scale data collection undertaken in this study will allow comparison and analysis of the occurrence of events between the various insulin treatment regimens. The same parameters will also be monitored for other injectable antidiabetic treatment regimens used during pregnancy.

The study is non-interventional. The assignment of patients to a particular therapeutic strategy is not decided in advance by a trial protocol but instead falls within current practice. Data will be collected in the context of routine practice, with very few exclusion criteria, and hence the results are expected to be more broadly applicable to the real-world population than those of typical RCTs.

The primary objective is to estimate the proportion of pregnancies in women treated with IDet, compared with other basal insulin regimens, which do not result in any of the following events: major congenital malformations, perinatal death or neonatal death (assessed at up to 4 weeks after delivery). The definitions of these and other key terms, within the context of this trial, are provided in Table 1.

**Table 1 Tab1:** Definitions of key terms

Term	Definition
Congenital malformation	A morphological defect of an organ, part of an organ or larger region of the body resulting from an intrinsically abnormal developmental process
Foetal macrosomia	Birth weight above 4 kg
Large for gestational age	Live born infant with birth weight >90th percentile for gestational age and sex according to local reference
Major malformation	A life-threatening structural anomaly or an abnormality likely to cause significant impairment of health or functional capacity and which needs medical or surgical treatment; examples are abnormalities likely to lead to serious handicap or likely to lead to major cosmetic defects (e.g., cleft lip) and which may require major surgery to repair (e.g., atrial septal defect or ventricular septal defect)

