### Study endpoints

The primary endpoint is the proportion of pregnancies in women treated with IDet, compared with other basal insulin regimens, which do not result in any of the following events: major congenital malformations, perinatal death or neonatal death (assessed at up to 4 weeks after delivery).

Key secondary endpoints relate to outcomes with IDet versus other basal insulin regimens for the mother, the fetus and the infant at 1 year of age. Maternal endpoints include the incidence of major hypoglycaemia during pregnancy, the proportion of pregnancies complicated by pre-eclampsia and metabolic control (measured as HbA_1c_). Perinatal outcome endpoints include the proportion resulting in fetal macrosomia, LGA, preterm delivery or spontaneous abortion. Infant endpoints assessed at 1 year of age include height, weight, the proportion with diabetes, and the proportion with changes (progression/regression) of major congenital malformations.

Safety data will also be collected in the pregnant women participating in the study, as well as in their offspring up to 1 year of age.

For analyses of the primary and secondary endpoints, only women treated with basal insulin will be included. However, information on all insulins and other injectable antidiabetic treatment regimens will be collected to facilitate comparison and analysis of outcomes in IDet-treated patients versus, for example, patients treated with an insulin pump.

Any change in basal insulin after the baseline visit will lead to exclusion from the statistical analyses of the primary and secondary endpoints, but not from the study. However, changes in dosage or dose interval, or add-on/removal of bolus insulin, oral antidiabetic drugs and/or glucagon-like peptide-1 (GLP-1) agonists, will not lead to exclusion from the analyses.

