### Determination of sample size

The sample size calculation was derived from the primary endpoint, based on patients with none of the three individual outcomes: major congenital malformations, perinatal death or neonatal death. The probability of this combination of endpoints is not known within the literature. However, based on data from a UK population study [10], which are in line with results from other European countries [1, 2, 4, 11–13], the proportion of pregnancies with any of the above outcomes is estimated at 8.2%: major congenital malformations, 4.5%; perinatal death, 3%; neonatal death, 0.9% (8.2% is computed under the assumption that the individual outcomes are independent). The proportion of pregnancies *without* any of the above outcomes is therefore estimated at 91.8%.

The goal is to be able to detect a difference of 3.5% between the proportions without the combined endpoint in the IDet group compared with the other basal insulin regimens group. Assuming a maximum 1:2 split between the two groups (IDet group: other basal insulin regimens group), a sample size of 1833 pregnancies is needed to have 80% power of achieving significance at a 5% level.

To achieve a total of 1833 pregnancies for the assessment of the primary endpoint, the planned number of patients to be included during the 5 years of the recruitment period is 3075. This number is based on the expectation that ~20% of pregnancies will result in a spontaneous abortion, ~10% will be treated with other antidiabetic injectables or will change basal insulin treatment and ~10% will be lost to follow-up, leaving 60% of pregnancies (i.e., 1833) assessable for the primary endpoint.

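### The only planned result on the scale of the 3.5-point goal is a crude difference with Fisher's exact test, which is not protected against confounding, and the article does not say whether it or the adjusted regression governs

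*Protocol article*

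**What the plan says.** Under Methods/design the study is non-interventional: "The assignment of patients to a particular therapeutic strategy is not decided in advance by a trial protocol". Study endpoints defines the target as a contrast of two proportions: "The primary endpoint is the proportion of pregnancies in women treated with IDet, compared with other basal insulin regimens".

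Statistical considerations then gives this endpoint two inferential results.

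- Adjusted: "The primary endpoint will be analysed using a logistic regression model that will include treatment group, study site, race, hypertension", followed by other factors and by covariates that include HbA1c at three times, age, body mass index and duration of diabetes.
- Crude: the proportion is computed in each group and "the absolute difference between these proportions calculated, along with the 95% CI", with a p-value "using Fisher’s exact test".

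One general rule covers both: "tests will be performed as two-sided tests with a significance level of 0.05". No ranking of the two results is given, and no risk difference derived from the model is described.

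Determination of sample size works on the absolute scale: "The goal is to be able to detect a difference of 3.5% between the proportions without the combined endpoint in the IDet group". The stated need is 1833 assessable pregnancies, split 1:2, for 80% power.

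**The concern.** Fisher's exact test compares two rows of a 2x2 table and takes no account of how the rows came about. Here they come from prescribing decisions. The Background section reports that higher HbA1c went with more perinatal deaths and malformations, and the long covariate list shows that the authors expect prognostic differences to matter. Yet the one estimate that answers the question posed in the sample size section, whether the groups differ by 3.5 points, leaves all of this out. The logistic model answers on the odds-ratio scale.

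Two errors are possible. A crude difference could reach significance with no drug effect, or confounding in the other direction could hide a real excess of events. The second is the more serious for a safety study requested by the regulator. With two p-values at 0.05 and no stated order, either could be quoted as the study's answer. The same section applies similar analyses to the other endpoints that are proportions, so the ambiguity may carry over to them.

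**Working it through.** **1. Event rate in the plan.** Determination of sample size gives 4.5%, 3% and 0.9%, taken as independent: 1 - 0.955 x 0.970 x 0.991 = 8.20%. This agrees with the stated 8.2%, or 91.8% event-free.

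**2. What the 1833 corresponds to.** Take event-free proportions of 95.3% (detemir) and 91.8% (other), a 1:2 split, two-sided 5% and 80% power. The pooled two-proportion formula is

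n(detemir) = [1.960 x sqrt(1.5 x P x (1 - P)) + 0.842 x sqrt(p1(1 - p1) + p2(1 - p2)/2)]^2 / 0.035^2,

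with P = (0.953 + 2 x 0.918)/3 = 0.9297. The two terms are about 0.614 and 0.242. Their sum squared is about 0.732, and 0.732/0.001225 gives 598. The total is 3 x 598 = 1794, within 3% of 1833. At 611:1222 the formula gives 80.9% power, and exact enumeration of Fisher's test gives 80.3%.

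The stated number is thus what a crude comparison of two proportions needs. The article does not name the test used for sizing. The match also depends on the 3.5 points running upwards from 91.8%: with 88.3% in either group, Fisher power at 611:1222 is 63-65%.

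**3. What confounding alone could do.** The documents give no baseline data by insulin, so these inputs are assumptions: no drug effect, 8.2% events in the other-insulin group, and one binary risk factor with risk ratio RR and prevalence p (detemir) and q (other).

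- Risk without the factor: b = 0.082 / (1 - q + q x RR)
- Risk under detemir: b x (1 - p + p x RR)
- Spurious difference: 0.082 minus that risk

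Example with RR 2, p 30%, q 50%: b = 0.082/1.5 = 0.0547; detemir risk = 0.0547 x 1.3 = 0.0711; difference = 1.09 points.

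| RR | p vs q | Spurious difference (points) | Fisher p <= 0.05 at 611:1222 |
|---|---|---|---|
| 1.5 | 30% vs 40% | 0.34 | 5.1% |
| 1.5 | 30% vs 50% | 0.66 | 6.9% |
| 1.5 | 20% vs 50% | 0.98 | 10.2% |
| 2 | 30% vs 40% | 0.59 | 6.4% |
| 2 | 30% vs 50% | 1.09 | 11.7% |
| 2 | 20% vs 50% | 1.64 | 22.0% |
| 2.5 | 30% vs 40% | 0.77 | 7.8% |
| 2.5 | 30% vs 50% | 1.41 | 17.0% |
| 2.5 | 20% vs 50% | 2.11 | 34.8% |

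With q at 50% the spurious difference is 0.7 to 2.1 points, or 0.66/3.5 = 19% to 2.11/3.5 = 60% of the target. With a 10-point imbalance it is 0.3 to 0.8 points, and the rejection rate hardly leaves 5%.

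**4. Can the listed model be standardised as it stands?** Three features stand in the way.

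- Diabetes type is not among its terms; the section mentions it only for descriptive splits.
- Major hypoglycaemia during pregnancy and HbA1c at the end of the first and second trimesters are measured after exposure has begun and may be affected by treatment.
- Study site is a factor with about 53 levels (Study organisation). Expected events are 1833 x 0.082 = 150, or 611 x 0.047 + 1222 x 0.082 = 129 under the planned effect. That is 2.4 to 2.8 events per site, so sites without events are likely.

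**The case against.** The strongest reply is that adjustment is already planned. The regression comes first and is what the endpoint is said to be analysed with; the crude proportions follow, as they usually do in a cohort report. On that reading the model governs and the difference only accompanies it. Which result is confirmatory, and how the interval is computed, are details that an article may leave to the analysis plan. This stands in part. A reader might infer that the study has no adjusted primary analysis, and that would be wrong. Silence on the ranking alone would not be a finding either. What remains is a stated choice: a named test without covariates is attached to the difference, on the very scale of the study's goal.

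A reader might also infer that the crude difference is confounded. The documents do not show that. The Background cites a series of 113 pregnancies with comparable glycaemic control under detemir and glargine, and Study organisation describes sites as having relatively similar routines. Neither excludes imbalance within sites or against other basal insulins, but the supportable statement is only that the comparison is not protected.

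Finally, one might object that Fisher's test yields no interval for a difference, so the CI and p-value could disagree. The sentence most naturally ties Fisher's test to the p-value alone. The interval method can be left to the analysis plan, and a borderline disagreement would be minor.

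**Conclusion.** The point holds in this limited form. An adjusted odds ratio for the primary endpoint will exist, but the only absolute difference, interval and p-value on the scale of the 3.5-point goal are crude, in a cohort whose treatment is not assigned by protocol, and the article does not say which result decides. The stated 1833 matches the crude comparison (80.3% Fisher power at 611:1222 for 95.3% against 91.8%).

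The illustrated bias of 0.7 to 2.1 points, with rejection in 7-35% of studies, rests wholly on the assumed risk ratios of 1.5 to 2.5 and prevalences of 20-30% against 50%. It shows what is possible and does not estimate the bias in this study. Smaller imbalances do little harm, and the direction is unknown.

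**What to change.** 1. State that the confounder-adjusted analysis is the primary one.
2. Report an adjusted risk difference with a delta-method or bootstrap 95% CI. It can be obtained by marginal standardisation (mean predicted risk with every woman set to detemir, minus the mean with every woman set to other basal insulin) or by propensity weighting.
3. Do not standardise the listed model unchanged. Restrict it to baseline or pre-exposure confounders, add diabetes type, leave out variables measured during pregnancy that treatment may affect, and handle site by country, a random effect or penalisation.
4. Present the crude proportions and their difference as descriptive, without Fisher's p-value as a primary test.
5. Say that the 80% power for 1833 refers to the crude comparison. The power of the adjusted analysis cannot be derived from the article.

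The cost is revised wording and somewhat more analysis work. No new data are needed, since diabetes type is already taken from the maternal medical history.

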### Treatment protocol and follow-up procedures

The frequency of visits will be determined by the individual study sites, and the data will be gathered as part of standard local routine. Only data collection at 1 month and at 1 year follow-up will be performed separately for the purpose of the study.

Data will be collected at various time points, including baseline (occurring as soon as the woman has discovered her pregnancy through a positive pregnancy test), standard routine visits throughout pregnancy, delivery (relating both to the mother and the neonate), 1-month follow-up and end of study (1-year follow-up) (Fig. 1). Postpartum follow-up at 1 month and 1 year will be performed using questionnaires (see Additional files 1 and 2) and telephone interviews. The 1-month follow-up will collect information on height, weight, neonatal death (yes or no), congenital malformations not detected at delivery, duration of exclusive/partial lactation and any adverse events (AEs) relating to the neonate. The 1-year follow-up will collect information on the duration of exclusive and any lactation, height, weight, diabetes in the infant (yes or no), changes in major congenital malformations and any AEs relating to the infant.

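### The stated adjustment of 1-year infant height and weight omits infant sex and age at measurement, a modest and nearly free loss of precision

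*Protocol article*

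**What the plan says.** The Study endpoints section names the outcomes: "Infant endpoints assessed at 1 year of age include height, weight, the proportion with diabetes", together with changes in major malformations. Height and weight are worded as plain measures.

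The Statistical considerations section gives the adjustment in three steps:

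- **Primary model, factors:** "treatment group, study site, race, hypertension, major hypoglycaemic events during pregnancy, folic acid intake and use of GLP-1 agonists during pregnancy as factors".
- **Primary model, covariates:** HbA1c at three times in pregnancy, then "age and body mass index at baseline, duration of diabetes, blood pressure and previous perinatal complications will be included as covariates". Age stands beside body mass index at baseline, so it is the mother's age.
- **Infant endpoints at 1 year:** "Factors and covariates will be as per the primary endpoint", followed by "Analyses regarding height and weight will also be adjusted for exclusive and/or partial lactation period".

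For continuous outcomes the section adds: "Means of the continuous endpoints will be compared between the two groups using an analysis of covariance model".

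On data collection, the section on treatment protocol and follow-up says: "Postpartum follow-up at 1 month and 1 year will be performed using questionnaires", and also names telephone interviews. Table 1 in Methods/design defines large for gestational age as "Live born infant with birth weight >90th percentile for gestational age and sex according to local reference".

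**The concern.** The list was drawn up for malformation and death and then carried over to growth. The authors did consider what height and weight need beyond it, and named lactation. They did not name the two infant characteristics one would expect to matter most for size at about 12 months: sex, and exact age on the day of measurement. At birth the same protocol does not read weight without them, since its large-for-gestational-age definition uses gestational age and sex.

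Variation that could be explained is therefore left in the residual. What is at stake is the sharpness of the growth comparison, in a study whose Discussion says that data on such infant outcomes are lacking.

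**Working it through.** **1. Is either variable in the list?** Every term in the primary model is maternal, apart from treatment group and study site. Lactation period is the only addition for height and weight. Infant sex and infant age at measurement are absent.

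**2. Group sizes for illustration.** The article gives no sample-size figure for height or weight. I borrow the primary-endpoint figure of 1833 pregnancies at 1:2, that is 611 and 1222. That figure is not in dispute. With 95.3% against 91.8%, two-sided 5%, 80% power, pooled variance and no continuity correction, the calculation gives 598 + 1196 = 1794, about 2% below 1833. Power at 611 and 1222 is 0.809. Fewer infants may have 1-year data, but the relative results below do not depend on the number.

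**3. Sex: share of variance.** The documents give no SD or sex difference. Assume a difference of d within-sex SD and equal numbers of boys and girls, with the residual SD given all other terms set to 1. The variance due to sex is d²/4.

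- Share of variance = (d²/4) / (1 + d²/4)
- Ratio of standard errors, without sex to with sex = √(1 + d²/4)
- Difference detectable with 80% power = (1.96 + 0.8416) × √[(1 + d²/4)(1/611 + 1/1222)] without sex. With sex in the model, √(1/611 + 1/1222) = 0.0495, and 2.8016 × 0.0495 = 0.139 SD.

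| d (assumed) | Share of variance | SE ratio | SE reduction if sex is added | Detectable difference without sex | With sex |
|---|---|---|---|---|---|
| 0.4 | 3.8% | 1.020 | 1.9% | 0.142 SD | 0.139 SD |
| 0.6 | 8.3% | 1.044 | 4.2% | 0.145 SD | 0.139 SD |
| 0.8 | 13.8% | 1.077 | 7.1% | 0.150 SD | 0.139 SD |

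**4. Age at measurement: precision.** Assume growth of g = 0.2 to 0.4 SD per month and an SD of age at measurement of s = 0.25 to 1 month. The extra variance is (g·s)², from 0.0025 to 0.16. Together with sex, the total variance relative to the fully adjusted analysis runs from 1 + 0.04 + 0.0025 = 1.04 to 1 + 0.16 + 0.16 = 1.32. The unadjusted analysis would thus need about 4% to 32% more infants for the same precision. The upper end requires all assumptions to be at their extremes.

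**5. Age at measurement: bias.** With study site in the model, the bias is g × (difference in mean age at measurement between insulin groups within sites). If that difference is 0, the bias is 0 and the error rate stays at 5%. At 0.25 month the bias would be 0.05 to 0.10 SD, and at 0.5 month 0.10 to 0.20 SD. Nothing in the documents indicates which value applies.

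**The case against.** **The model may not be closed.** The carry-over sentence directly follows one on proportions and logistic regression, and the analysis-of-covariance sentence names no covariates. Derivation of standardised scores and the full model are commonly left to an analysis plan, which is not shown. This has some force. Yet the lactation sentence says height and weight will also be adjusted, which presupposes the list just cited, and it names one extra term specific to these outcomes. Improving a stated list is a fair request, even if the unseen plan may already do so.

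**Timing bias.** A reader might infer that uneven timing of the 1-year contact across sites or countries could pass as a growth difference between insulins. The documents do not support that. Study site is a listed factor and absorbs mean differences between sites, and hence between countries. What remains is a difference between insulin groups within the same site. The article gives no sign of one, and it says that the 1-month and 1-year data are collected separately for the study, so these contacts are not tied to routine visits.

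**No measurement window.** A reader might also infer that the 1-year contact has no age window or date field. The article states none, but Fig. 1 and the two questionnaires are not available here, and such details often sit in the full protocol. No conclusion is drawn from their absence.

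**Small effect.** Infant sex should not depend systematically on the mother's basal insulin, so omitting it costs mainly precision, and the gain in step 3 is modest. This stands in full.

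**Conclusion.** The point holds as a precision matter. The stated adjustment for 1-year height and weight leaves out infant sex and age at measurement, although infant sex is already required elsewhere in the protocol. On the assumed sex difference of 0.4 to 0.8 SD, adding sex moves the detectable difference from 0.142–0.150 SD to 0.139 SD. Any further gain from age depends on how widely ages at measurement spread, which is unknown.

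The material does not establish bias in the growth comparison. That would take a within-site timing difference between insulin groups, so the bias figures in step 5 are conditional arithmetic and not a prediction. All magnitudes are assumptions, because the article gives no SDs, sex differences or growth rates. Only two secondary endpoints are touched. This is a nearly free improvement and not an error that threatens the study's conclusions.

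**What to change.** Either add infant sex and exact age at measurement to the analysis of covariance for 1-year height and weight, beside the existing terms, or analyse both outcomes as age- and sex-standardised scores on one common reference for all countries. Compute age from the birth date and the recorded date of measurement. If the 1-year questionnaire has no field for that date, add one.

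The cost is a sentence in the analysis section and at most one data field. Sex must already be held for the large-for-gestational-age endpoint, and the birth date should follow from the delivery data. No change to the primary endpoint, the sample size or the conduct of the study is needed.
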